### 4QM protocol

3.2

The OPC+4QM interventions will be provided once a week with fourteen 60-min sessions (ten sessions for OPC + four sessions for 4QM). The follow-up period will be one month. Four sessions of 4QM will be scheduled in four quadrants during the OPC sessions to achieve the identified goals. After analyzing each goal in the OPC approach by using collaborative performance analysis, 4QM will be employed for the plan action of that goal. Also, the principles of teaching and learning will be present both in OPC and 4QM sessions, but in Four sessions of the 4QM, various cognitive and physical learning strategies are organized and implemented in the form of 4 quadrants.

The first 4QM intervention sessions along with the first OPC session introduce the 4QM, its components, and presents the printed forms of 4QM for each goal to the mothers. The second, third, and fourth sessions of 4QM interventions will be done along with the OPC sessions related to the first to third selected goals to train and implement the goals in the format of 4QM.

Integration of two continua is used in 4QM given the (i) directness of the strategy (first direct and then indirect) and (ii) clustering the initiation source (first the mother as a facilitator and then the child as a learner) to prompt teaching-learning strategies given the needs of the child. In the quadrant 1, the characteristics and requirements of the task are determined. Strategies including demonstration, explicit instruction/explanation, lower-order questions, and physical patterning, will be initiated by the mother (facilitator) directly. In the quadrant 2, the child will be supported in carrying out tasks through involving them in decision-making processes. Indirect strategies including feedback, higher-order questions, nonverbal prompts, physical prompts, and think-aloud modeling will be initiated by the mother (facilitator). The quadrant 3 will focus on identifying the steps of the activity and child (learner) driven processes and highlights direct strategies like mnemonics, priming, visual cues, verbal self-instruction, and kinesthetic self-prompting that a child (learner) might overtly use to improve their performance through concentrating on key points. Quadrant 4 indicates autonomous performance by the child (learner) through indirect strategies like self-instruction, self-questioning, mental imagery, problem-solving, self-monitoring, and automaticity [44,55,56] (Table 2).

**Table 2 tbl2:** The four-quadrant model of facilitated learning in the current study.

Quadrants	Key Concept	Strategies
Quadrant1 (Direct, Mother-Initiated)	Task Specification	• Explicit instruction/explanation
		• Demonstration
		• Physical patterning
		• Lower order questions
Quadrant 2 (Indirect, Mother-Initiated)	Decision-making	• Higher order questions
		• Feedback
		• Physical prompts
		• Nonverbal prompts
		• Think-aloud modelling
Quadrant 3 (Direct, Child-Initiated)	Key points	• Priming
		• Mnemonics
		• Verbal self-instruction
		• Visual cues
		• Kinesthetic self-prompting
Quadrant 4 (Indirect, Child-Initiated)	Autonomy	• Mental imagery
		• Self-instruction
		• Self-questioning
		• Self-monitoring
		• Problem solving
		• Automaticity

### Goal setting

3.3

Mothers need to speak about their child's activities outside school and to set three objectives for the intervention and two extra goals (transfer goals) as the measure of outcome for the transfer [41]. The occupational therapist will ask mothers to assign a point to each goal with the 10-point scale scoring system of the COPM (Canadian Occupational Performance Measure). To make mothers more familiar with the details of activities outside school, during the semi-structured interview COPM, CPAS-P (Children Participation Assessment Scale -Parent Version), including 71 items of different areas of children's occupational performance will be provided to them. In addition, simultaneous with the COPM, the Goal Attainment Scale (GAS) will be used to examine the achievement of the desired goals.

## Data collection

4

### Characteristics of participants

4.1

Demographic information of mothers such as age, job, and level of education and demographic information of children such as age, school grade, and gender will be collected.

The WISC-IV (Persian version of the Wechsler Intelligence Scale for Children-Fourth Edition) will be used to test the intelligence of the children with SLD in this study. Perceptual reasoning, Verbal comprehension, processing speed, working memory, and full intelligence scales are evaluated by the test. The validity and reliability of the tool for Iranian children in the age range 6–16 years have been confirmed [57]. Furthermore, the WISC-IV scales and cognitive assessment system (CAS) test are acceptably correlated for children suffering learning disorders. There is also concurrent validity between the two tests and the scales [58].

The Child Symptom Inventory-4 (CSI-4) will be used to screen children aged 5–12 years for eighteen behavioral and emotional symptoms and measure comorbidity. This 4-point Likert scale is based on the DSM-V and demonstrates the frequency of psychiatric symptoms seen in the children [59]. The questionnaire has two (parent and teacher) versions. The parent version will be used in this study. Test-retest reliability of the Persian version of CSI-4 (parent version) for eleven disorders is 0.29–0.76 [60].

The DASS-21 (Depression, Anxiety, and Stress Scale- 21 Items) will be utilized to screen the mental health of participating mothers. The DASS-21 contains 21 items with three dimensions (anxiety, depression, and stress) [61]. The DASS-21 has a desirable test-retest reliability (0.740–0.881) and validity (Cronbach's alpha of stress = 0.67, anxiety = 0.49, and depression = 0.70) was reported for the Persian version of DASS-21 [62].

### Outcome measures

4.2

The results will be examined before, immediately after, and one month of the intervention. Moreover, the psychometric properties of outcome assessment tools will be checked by professionals previously trained. Assessors (occupational therapists) will be not aware of group allocation and only will be aware of the allocation as the main investigator.

#### Measures of the primary outcome—the first and second study goals

4.2.1

##### Occupational performance and satisfaction

4.2.1.1

The COPM (Canadian Occupational Performance Measure) will be utilized for scoring occupational performance and satisfaction by the mothers of children with SLD. As a semi-structured interview, COPM helps mothers identify their goals. The participant is asked to score performance and satisfaction with selected goals related to activities outside school on a 10-point score (ranging from 1 = not satisfied to 10 = satisfied) [63]. Two-point change or more overtime are considered clinically relevant. Test-retest reliability for COPM is measured for various populations and it varies 0.84 to 0.92 [64]. The content validity of the Persian version of the COPM is (80.95 ± 0.222) [65].

##### Achievement of objectives

4.2.1.2

Goal Attainment Scale will be used to quantify progress towards selected goals related to activities outside school by the mothers of children with SLD. This scale is useful in the family-centered intervention where parents, as ‘experts’, can make important contributions to their children's success [66]. The GAS includes five scores (−2 to +2). A score of zero means the expected level of performance after some time, scores of −2 and −1 indicate reaching a level lower than expected, and scores of +2 and + 1 indicate reaching a level higher than expected [67]. The inter-rater reliability of the scale is 0.67 in different populations and content validity (r = 0.86) has also been reported for pediatric disorders [68].

##### Participation in activities outside of school for children

4.2.1.3

The CPAS-P (Children Participation Assessment Scale in Activities Outside of School-Parent Version) will be used to assess participation by children outside school in two key life situations (community and home) [5]. This tool is designed for children in the 6–12 years age range. The tool contains 71 items categorized in eight areas of occupations including BADL, IADL, leisure, play, work, education, social participation, and sleep/rest. The parents should report the diversity of activities for each activity that the child performs [6]. Intraclass correlation coefficient (ICC) and Cronbach's alpha for the Persian version of CPAS-P were 0.91–0.94 and 0.90 to 0.95, respectively [69].

##### Transfer of skills

4.2.1.4

The transfer goal (fourth and fifth goals) will not be covered in the intervention. The occupational satisfaction and performance in the children on the transfer goal will be measured using COPM's scoring system. Furthermore, achievement of these objectives will be measured using GAS at baseline, post-intervention, and after a 1-month follow-up. Capistran and Martini reported the use of extra goals to evaluate transfer with children [70].

#### Secondary outcome measures—the third and fourth study objectives

4.2.2

##### Executive function skills for children

4.2.2.1

The BRIEF (Behavior Rating Inventory of Executive Function)-Parent Form will be utilized to determine the outcome. The mothers will rate their children's behavior and metacognitive function in the natural context (home or school). This questionnaire is designed for children in the 5–18 years age range and consists of 86 items categorized into eight separate subscales (Working Memory, Initiate, Organization of Materials, Plan/Organize, Inhibit, Monitor, Shift, and Emotional Control). The total score of these subscales is called the Global Executive Composite (GEC) that is divided into two broad scales of Behavior Regulation Index (BRI) and Metacognition Index (MCI) for scoring [71]. The GEC, BRI, and MCI scale test-retest coefficients were 0.80, 0.81, and 0.83, respectively [72]. As to the internal consistency of the BRIEF (parent-form) Persian version, Cronbach's alpha for GEC was 0.86 [73].

##### Academic achievement of children

4.2.2.2

Grade Point Average (GPA) will be used to measure academic achievement of children in this study. This score is the average point in the three subjects of mathematics, reading, and spelling; which are three courses in which children with SLD are more likely to have academic failure [15]. Mothers are required to receive their child's GPA from the teacher of the school before, after, and one month after the intervention.

##### Self-efficacy of mothers

4.2.2.3

The Sherer General Self-Efficacy Scale (SGSES) will be used to measure the self-efficacy of mothers of children with SLD. It features a five-point rating scale with 17 items, so that the higher the score the better the self-efficacy. The internal consistency and test-retest reliability of this scale are 0.86 and 0.76 respectively [74]. Confirmation of several predicted conceptual relationships between the Sherer General Self efficacy subscales with personal characteristics like self-esteem provided evidence of construct validity and internal-external control [75].

## Data management

5

An assistant will enter the data into SPSS-Vesrion22®. The participants' data will be stored on a password-protected lab computer. According to the Research Ethics Committee, all data including evaluation forms, intervention checklists will be kept in in the laboratory for five years.

### Adverse events

5.1

During the course of assessment or intervention, we will record all adverse events like pain, discomfort, and disagreement. In the case that the adverse events are related to the study plans, modification or termination of activities or sessions can be considered. The mothers will undergo a medical check to examine any significant or unexpected side effect.

### Data analysis

5.2

To analyze the first and second objectives, (a) mean and median changes in the satisfaction and occupational performance scores of the first three goals chosen by the mothers from the COPM from baseline (t_1_) to post-intervention (t_2_) and a 1-month follow-up (t_3_); (b) mean and median changes in the scores of the diversity of participation in activities outside school provided by CPAS-P from t_1_ to t_2_ and t_3_; (c) mean and median changes in goal attainment in the scores of the first three goals chosen by the mothers on GAS from t_1_ to t_2_ and t_3_; and (d) mean and median changes on occupational performance and satisfaction and goal attainment in the scores on COPM and GAS on transfer goals (The fourth and fifth goals chosen by the mothers) to analyze the transfer of skills from t_1_ to t_2_ and t_3_ will be used.

To analyze the third and fourth objectives (a) mean and median changes in the total score of executive function on the BRIEF from t_1_ to t_2_ and t_3_; (b) mean and median variations in educational status on the transcript from t_1_ to t_2_ and t_3_; and (c) mean and median variations in the self-efficacy of mothers on the SGSES from t_1_ to t_2_ and t_3_ will be used.

### Statistical methods

5.3

Qualitative and quantitative variables are explained using relative and absolute frequencies, as well as central tendency, variance, and position measurements. To examine the homogeneity in characterization variables (age, gender, child's level of education, parent's level of education-possible confounding variables) chi-square test for qualitative variables and *t*-test for quantitative variables will be used. The Shapiro-Wilk test will be used to assess the normality of variables. Analysis of variance (ANOVA) will be utilized for comparison of the efficacy of OPC+4QM versus OPC on the primary and secondary results. The multivariate models include time and group interactions and Intention to Treat (ITT) will be used for participants who do not complete the interventions; pre-test score will be used instead of the post-test score [76]. A 2 tailed p < 0.5 will be considered significant and effect size (partial η^2^) will be calculated using R software-version 3.5.0.

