The primary objectives are to examine the efficacy of the OPC approach with and without 4QM on occupational performance, satisfaction, and achievement of goals (transfer and trained goals) and participation in activities outside school for SLD children. In addition, the efficacy of OPC+4QM versus OPC on similar results will be examined. The second-level goals are to examine and compare OPC+4QM and OPC efficacy on executive performance (such as organization, cognitive flexibility, and mental planning); to investigate and compare academic achievement; and to examine and compare self-efficacy in mothers of children with SLD. The trial's hypotheses state that OPC+4QM and OPC are effective in improving outcomes in children and parents and the experimental group submitted to OPC+4QM have better effects on the main and secondary outcomes immediately and one month after the interventions.

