### Sample size

2.4

Sample size calculations were performed in G-Power software based on the COPM test as the main variable of the study. A two points change in this variable between the intervention and control group will be considered as significant difference [49]. Considering α-value of 5%, the power of 95%, the standard Cohen's effect size of 1, the required sample size was obtained equal to 27 for each group, and assuming 10% dropout rate, 30 subjects were selected for each group. Furthermore, since the sample size was calculated based on the primary outcome, the study is anticipated under-powered for addressing secondary outcomes.

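### The arm comparison is an ANOVA on changes from baseline with no baseline covariate: valid, but less precise than baseline adjustment, and the stated 95% power is not assured under it

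*Protocol article*

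**What the plan says.** All references are to the protocol article.

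- **Statistical methods (5.3)** names the test: "Analysis of variance (ANOVA) will be utilized for comparison of the efficacy of OPC+4QM versus OPC". It adds: "The multivariate models include time and group interactions". No baseline score is named as a covariate.
- **Data analysis (5.2)** defines the quantities of interest as changes from t1 to t2 and t3. For the COPM these are "mean and median changes in the satisfaction and occupational performance scores of the first three goals", and the other measures follow the same form.
- **Introduction (1)** gives the hypothesis: the OPC+4QM arm is expected to "have better effects on the main and secondary outcomes immediately and one month after the interventions". That is an arm difference at t2 and another at t3.
- **Sample size (2.4)** is a simple two-group calculation: "Considering α-value of 5%, the power of 95%, the standard Cohen's effect size of 1". The target is worded as follows: "A two points change in this variable between the intervention and control group will be considered as significant difference". The result is that "the required sample size was obtained equal to 27 for each group", raised to 30 for dropout.

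Taken together, sections 5.2 and 5.3 strongly suggest a repeated-measures ANOVA with baseline as one of three levels of time. The text does not say so in words.

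**The concern.** Every outcome is measured at baseline, so a baseline-adjusted comparison needs no extra data. The planned comparison uses the baseline only by subtraction, or by the equivalent interaction contrast. That gives up precision whenever the baseline-to-post correlation is below 1 (with equal SDs). With 27 to 30 per arm the loss can matter, and more so for the secondary outcomes, for which section 2.4 already expects low power.

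Two further points follow.

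- An interaction over three visits is a test on two degrees of freedom. A significant result does not say whether the arms differ at t2, at t3 or at both, and partial eta-squared is not a difference in COPM points.
- The sample size was worked out for a two-sample t-test, while the planned analysis is a change or interaction contrast. The two have the same power only under particular assumptions about the SD and the correlation, and the document states neither.

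**Working it through.** **Inputs**

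- Alpha 5%, power 95%, d = 1, 27 per group, 10% dropout: section 2.4.
- Two-sided testing: section 5.3, "A 2 tailed p < 0.5 will be considered significant". The printed level conflicts with the 5% in section 2.4. That is a separate matter, and 0.05 is used here.
- Target of 2 COPM points: section 2.4. With d = 1 this implies an SD of 2. The section does not say whether that is the SD of a post score or of a change.
- r, the correlation between baseline and post-treatment score: not given. Values from 0.2 to 0.7 are assumed. The 0.84 to 0.92 in section 4.2.1.1 is test-retest reliability, which is a different quantity.

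**Step 1. Reproduce the plan's figure.** For a two-sided two-sample t-test the noncentrality is d × √(n/2) = 1 × √13.5 = 3.674 on 52 degrees of freedom, and power is 0.950. With 26 per group it is 0.942. So 27 is right, and 27/0.9 = 30.

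**Step 2. Compare variances.** With the same SD σ at each visit:

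- change score: 2σ²(1 − r)
- baseline-adjusted score: σ²(1 − r²)
- ratio, adjusted to change: (1 − r²) / [2(1 − r)] = (1 + r)/2

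This gives 0.65 at r = 0.3, 0.75 at 0.5 and 0.85 at 0.7. The standard error falls to √0.65 = 0.81, √0.75 = 0.87 and √0.85 = 0.92 of the change-score value. If the SDs differ (σ₀ before, σ₁ after), the change variance exceeds the adjusted variance by (σ₀ − rσ₁)², which is never negative.

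**Step 3. Power at 27 per group if d = 1 is on the post-score SD.** The effective d is 1/√[2(1 − r)] for change and 1/√(1 − r²) after adjustment. At r = 0.3 these are 1/√1.4 = 0.845 and 1/√0.91 = 1.048. For the interaction over t1 to t3, with a 1-SD arm difference at both t2 and t3 and equal correlations r between all visits, the noncentrality is 13.5 × (2/3)/(1 − r) = 9/(1 − r) on 2 and 104 degrees of freedom.

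| r | Change score | Omnibus interaction | Baseline-adjusted | n per group for 95%, change | n per group for 95%, adjusted |
|---|---|---|---|---|---|
| 0.2 | 0.813 | 0.850 | 0.957 | 43 | 26 |
| 0.3 | 0.862 | 0.896 | 0.966 | 38 | 25 |
| 0.4 | 0.909 | 0.938 | 0.976 | 33 | 23 |
| 0.5 | 0.950 | 0.971 | 0.986 | 27 | 21 |
| 0.6 | 0.981 | 0.991 | 0.995 | 22 | 18 |
| 0.7 | 0.996 | 0.999 | 0.999 | 17 | 15 |

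The change-score and adjusted columns are for a single post-treatment visit. The adjusted column ignores the one degree of freedom spent on the covariate, which is negligible here.

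**Step 4. Power if d = 1 is on the change-score SD.** The change-score contrast then has power 0.950 at every r, by construction. The adjusted analysis has effective d = 1/√[(1 + r)/2], and power 0.994 at r = 0.3, 0.986 at 0.5 and 0.974 at 0.7.

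**The case against.** The strongest reply is that the planned analysis is valid and may be fully powered. Section 4.2.1.1 describes the two-point criterion as change over time, so d = 1 on the change-score SD is a natural reading of section 2.4. On that reading 95% is met at every r. Even on the post-score SD it is met from r = 0.5 upwards, and the omnibus interaction is already at 0.938 at r = 0.4. Nothing in the document supports a low r in particular. All of this stands, and it rules out saying that the trial is underpowered.

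The figures above use 27 complete cases, whereas section 5.3 keeps non-completers with the pre-test score substituted. This is a fair qualification. With all 30 per group followed up, the change-score contrast on the post-score SD reaches 0.896 at r = 0.3 and 0.968 at r = 0.5. With 30 per group, 10% carried forward and no mean change in controls, it is 0.851 and 0.941. The pattern is the same.

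Section 5.2 lists changes to t2 and to t3 separately, and follow-up contrasts are often left to an analysis plan. This softens the point about the omnibus test but does not remove it, because the only test that the article names for the arm comparison is the ANOVA.

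Three stronger readings are tempting, and the text does not support them:

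- **The group main effect, diluted by the pre-treatment visit, is the efficacy test.** Section 5.3 points to time-by-group terms and section 5.2 to changes.
- **Baseline imbalance is handled only by the chi-square and t tests on characteristics such as age and education.** Changes from t1 and the interaction both use each participant's own baseline score.
- **Covariates will be picked from those tests.** The section uses them to examine homogeneity and mentions no selection.

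**Conclusion.** The point holds as a matter of efficiency and clarity, not validity. Naming the baseline score as a covariate would cut the variance of the arm difference to (1 + r)/2 of the change-score variance, a reduction of 35% at r = 0.3, 25% at 0.5 and 15% at 0.7. This assumes equal SDs before and after treatment.

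A reader might infer that the 95% power is missed. The document supports only that it is not assured. The shortfall needs both d = 1 on the post-score SD and r below about 0.5. At r = 0.3 power would then be about 86% for the change-score contrast and about 90% for the omnibus interaction. If either condition fails, the planned analysis reaches about 95% or more. Baseline adjustment keeps power at about 95% or higher on both readings of the SD over the assumed range of r.

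Separately, a three-level interaction does not by itself answer the two visit-specific hypotheses in the Introduction. That baseline is one of those three levels is a strong inference from sections 5.2 and 5.3, not stated text.

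**What to change.** In Statistical methods, replace the ANOVA sentence with a model that takes t2 and t3 as the outcomes. Use a mixed model with arm, visit, arm-by-visit and the baseline value of the same measure as covariate, or an ANCOVA at each visit with the same covariate. Report the adjusted arm difference with its 95% confidence interval at t2 and at t3, in the units of each measure. Partial eta-squared can stay as a supplement.

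In Sample size, add one sentence saying whether d = 1 refers to the SD of the post score or of the change, and what baseline-to-post correlation is assumed.

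The cost is wording only. The baseline measurements are already scheduled, and neither the sample size nor the conduct of the trial changes.

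### Substituting the pre-test score for non-completers is labelled ITT, but it assumes zero change and does not match the sample size; the cost depends on control-arm change and on how non-completion splits

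*Protocol article*

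**What the plan says.** Section 5.3 (Statistical methods) specifies ANOVA with time and group interactions and says that ITT will be used "for participants who do not complete the interventions; pre-test score will be used instead of the post-test score". The trigger is not completing the intervention; the sentence does not mention a missing assessment. The article states no other rule for missing scores.

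Section 2.4 (Sample size) rests on COPM: "A two points change in this variable between the intervention and control group will be considered as significant difference". With 5% alpha, 95% power and "the standard Cohen's effect size of 1", "the required sample size was obtained equal to 27 for each group"; then, "assuming 10% dropout rate, 30 subjects were selected for each group".

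Three other places bear on the point. The objectives at the end of the Introduction hypothesise that OPC+4QM and OPC alone both improve outcomes. Sections 3.1 and 3.2 give ten sessions for OPC and fourteen for OPC+4QM. Section 4.2.1.1 treats a COPM change of two points or more as clinically relevant.

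**The concern.** Intention-to-treat means analysing every randomised mother in her allocated arm on the outcome she had. The rule keeps her in her arm but puts her baseline in place of her outcome. A mother who stops after session 8 and still attends the post-intervention assessment would, on the literal wording, lose her observed score. If only missing scores are meant, each is still replaced by a single value that assumes no change and carries no uncertainty. That sits badly with a protocol that expects improvement in both arms.

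The rule also departs from the logic of the sample size. Adding 10% for dropout protects power if dropouts are absent from the analysis and 27 per arm remain. Here they stay in, pull each arm's mean towards zero and, when the mean change is large, add spread. The comparison of arms then depends partly on who stops attending.

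**Working it through.** **Inputs from the protocol.** Difference 2 COPM points; standardised effect 1, hence an implied SD of 2 (not stated itself); two-sided alpha 0.05; 27 per arm, 30 after 10% dropout; 1:1 allocation. Section 5.3 prints "A 2 tailed p < 0.5 will be considered significant", which conflicts with the 5% in section 2.4. That is a separate matter, and 0.05 is used here.

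**Assumptions.**
- Control-arm mean change *m* is not stated, so it is ranged from 0 to 4 points.
- Non-completion is taken as the planned 10%, and as 15% versus 5% in each direction.
- Non-completers are taken to have the same true change as completers.
- The comparison is of baseline-to-post-test change with SD 2, equivalent to the two-time-point group-by-time test.

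**Step 1: the plan's own figure.** A two-sample t-test with effect size 1 and two-sided alpha 0.05 has power 0.942 at 26 per arm and 0.950 at 27. Then 27 / 0.9 = 30. Both stated figures reproduce. Analysing only 27 completers per arm, with dropout unrelated to outcome, keeps 95%; 30 observed per arm would give 96.8%.

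**Step 2: formulas under the rule.** With non-completion p_E and p_C, and non-completers' change set to 0:
- difference = (1 − p_E)(m + 2) − (1 − p_C)m
- variance, experimental arm = (1 − p_E)·4 + p_E(1 − p_E)(m + 2)²
- variance, control arm = (1 − p_C)·4 + p_C(1 − p_C)m²

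**Step 3: 10% in each arm, m = 2.** Difference = 0.9 × 4 − 0.9 × 2 = 1.8. Variances = 3.6 + 0.09 × 16 = 5.04 and 3.6 + 0.09 × 4 = 3.96; their mean is 4.50, so SD is 2.12. Effect size = 1.8 / 2.12 = 0.849, and power at 30 per arm is 89.8%.

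| Control change m | Difference | Power, random 10% | Power, exactly 3 of 30 per arm |
|---|---|---|---|
| 0 | 1.8 | 94% | 95% |
| 1 | 1.8 | 93% | 94% |
| 2 | 1.8 | 90% | 92% |
| 3 | 1.8 | 85–86% | 90% |
| 4 | 1.8 | 80% | 86% |

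The random column is the formula confirmed by simulation; the last column is simulated. By the formula, restoring 95% under the rule would take about 32 per arm at m = 0, 38 at m = 2 and 43 at m = 3.

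**Step 4: unequal non-completion, m = 2.**
- 15% in OPC+4QM, 5% in OPC: 0.85 × 4 − 0.95 × 2 = 3.4 − 1.9 = 1.5. Variances are 5.44 and 3.99, effect size 0.69, power about 75%.
- 5% in OPC+4QM, 15% in OPC: 0.95 × 4 − 0.85 × 2 = 3.8 − 1.7 = 2.1, an overstatement.

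**Step 5: no true difference, m = 2.**
- 15% versus 5%: 0.85 × 2 − 0.95 × 2 = −0.2 points; simulated type I error about 7%.
- Equal non-completion: 0.9 × 2 − 0.9 × 2 = 0, so no bias. With exactly 3 of 30 per arm the test is slightly conservative (about 4%).

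**The case against.** **Overwriting.** The sentence is condensed, and section 2.4 speaks of dropout, so the authors may mean only mothers with no post-test score. The text does not say that observed scores will be thrown away. This stands: the literal reading is available but not certain, and the wording needs clarifying. The zero-change assumption remains on either reading.

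**Loss of the stated power.** A reader might infer that the rule always forfeits 95%. It does not. The loss depends on a control-arm change that the protocol never gives, and it is close to nil if controls do not change. Variance is not always inflated either: at m = 0 the mean within-arm variance is (3.96 + 3.60) / 2 = 3.78, below 4.

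**Bias against OPC+4QM.** This too is tempting, because that arm has more sessions. The documents give no arm-specific non-completion, and section 3.2 schedules the 4QM sessions during and along with the OPC sessions. Four extra sessions are clear; a longer course is not. Non-completion could differ by arm, but nothing shows that it will, and the reverse split inflates the effect.

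**Extreme scenarios.** At m = 4, a 15% versus 5% split takes power to about 50% and, with no true difference, type I error to about 11%. With a true difference of 2, that means a mean gain of 6 points in the experimental arm on a 1–10 scale, with no ceiling modelled. No conclusion should rest on it.

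**The alternative is not assumption-free.** A mixed model assumes missing at random. If mothers leave because they see no benefit, it can overstate improvement. That is a reason to keep pre-test substitution as a sensitivity analysis, though not as the main method.

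**Conclusion.** The point holds in conditional form. The rule is stated, is not what ITT means, contradicts the expectation that both arms improve, and does not fit a sample size built on 27 analysed per arm. The sample-size arithmetic itself is correct.

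At the planned, balanced 10% the cost is modest: the expected difference falls by a tenth, and power falls by roughly 3 to 5 percentage points if controls improve by the clinically relevant 2 points. Larger harm, in either direction, requires unequal non-completion, and it grows with control-arm improvement. All figures rest on SD 2, a true difference of 2 and non-completers changing as completers do. If non-completers truly did not change, the rule introduces no bias.

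Severity: should be fixed. The documents do not support a claim that the trial is certain to be underpowered or biased in a known direction.

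**What to change.** Reword section 5.3 to say that:
- the post-intervention and one-month assessments are sought from every randomised mother, whatever number of sessions she attended;
- no observed score is replaced;
- all mothers are analysed as allocated, with a likelihood-based mixed model on the observed scores at both time points, assuming missing at random given baseline and earlier scores;
- pre-test substitution is a sensitivity analysis only, because missing at random may fail if mothers leave for lack of benefit.

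With this change, the 27-plus-dropout reasoning in section 2.4 again fits the analysis. The cost is revised wording, a little more analysis work and the effort of assessing mothers who stop attending. SPSS and R, both already named, can fit the model.

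### The analysis section sets significance at two-sided p < 0.5, ten times the 5% alpha behind the sample size

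*Protocol article*

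**What the plan says.** Section 5.3, Statistical methods, plans an ANOVA comparison of OPC+4QM with OPC on the primary and secondary outcomes and closes with the decision rule: "A 2 tailed p < 0.5 will be considered significant".

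Section 2.4, Sample size, works from a different level: "Considering α-value of 5%, the power of 95%, the standard Cohen's effect size of 1". From these inputs it reports that "the required sample size was obtained equal to 27 for each group" and then, "assuming 10% dropout rate, 30 subjects were selected for each group". The effect size is tied to the COPM: "A two points change in this variable between the intervention and control group will be considered as significant difference".

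These are the only two places where the article gives a significance level. Section 2.4 does not say whether its 5% is one-sided or two-sided. Section 5.3 says its threshold is two-sided.

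**The concern.** The threshold in section 5.3 decides whether adding 4QM to OPC is declared effective, and it covers every primary and secondary outcome. It is ten times the alpha used to size the trial. Under a two-sided p < 0.5 rule, an add-on with no effect would be declared different from control in half of all tests.

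This is a value stated wrongly, so a fuller protocol or an analysis plan that is not shown would not cure it. The article is the public record against which the eventual analysis will be read. While it contradicts itself, a threshold other than 5% could be presented as prespecified.

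**Working it through.** **Inputs.** All come from the article: alpha 5%, power 95%, d = 1, 27 per arm and 10% dropout (section 2.4); 1:1 allocation (section 2.5); two-sided p < 0.5 (section 5.3). No SD is given. A 2-point COPM difference with d = 1 implies SD = 2/1 = 2 points.

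**Step 1: reproduce the stated sample size.** For a two-sample t-test with n per arm, df = 2n − 2, the noncentrality is d·√(n/2), and power is the probability that |T| exceeds t(1 − α/2, df). With n = 27, df = 52, noncentrality √13.5 = 3.67 and critical value 2.007, power is 0.9501. Solving for 95% power gives n = 26.99, so 27. Dropout: 27/(1 − 0.10) = 30. Both stated figures reproduce.

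**Step 2: find which alpha yields 27.**

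| Alpha | n per arm for 95% power, d = 1 | Power with 27 per arm |
|---|---|---|
| 0.05, two-sided | 26.99 → 27 | 95.0% |
| 0.05, one-sided | 22.4 → 23 | 97.6% |
| 0.5, two-sided | 10.8 → 11 | 99.9% |

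The normal approximation, n = 2(z₁₋α/₂ + z₀.₉₅)²/d², agrees closely. At two-sided 0.05 it is 2(1.960 + 1.645)² = 26.0. At two-sided 0.5 it is 2(0.674 + 1.645)² = 10.8. Of the three alphas, only two-sided 0.05 gives the stated 27.

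**Step 3: false-positive rate of the printed rule.** Under the null hypothesis a two-sided p < 0.5 rule rejects 50% of the time by definition. In 100,000 simulated null trials with 27 per arm, a t-test rejected in 49.8% at p < 0.5 and in 5.1% at p < 0.05.

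**Step 4: smallest observed difference that would be significant.** This is t(1 − α/2, 52)·√(2/27), with √(2/27) = 0.272.

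- At p < 0.5: 0.679 × 0.272 = 0.18 SD, or about 0.37 COPM points if SD = 2.
- At p < 0.05: 2.007 × 0.272 = 0.55 SD, or about 1.09 COPM points.

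The article itself treats 2 points as the difference that matters.

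**Step 5: several outcomes together (illustration only).** Section 5.2 lists seven primary measures: COPM performance, COPM satisfaction and GAS on the trained goals, the same three on the transfer goals, and CPAS-P. The number of tests and their correlation are assumptions. The table gives the chance of at least one false positive at p < 0.5.

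| Pairwise correlation | 7 tests (one per measure) | 14 tests (two visits each) |
|---|---|---|
| 0.3 | 0.99 | 0.9998 |
| 0.5 | 0.98 | 0.999 |
| 0.8 | 0.90 | 0.97 |
| 0.9 | 0.80 | 0.88 |

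At p < 0.05 and correlation 0.5 the figures are 0.23 and 0.35. That remaining inflation is a separate multiplicity question, which correcting the threshold does not settle.

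**The case against.** The strongest reply is that this is a dropped zero. Section 2.4 fixes alpha at 5%, the sample size reproduces at that value, and few analysts would apply a threshold of 0.5. On that view the 50% rate describes a rule that nobody intends to use. Most of this stands: 0.5 is very probably a misprint, the sample size is sound, and the article does not show that the investigators mean to use 0.5. But the misprint sits in the only sentence that fixes the success criterion, and nothing in the article corrects it.

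Three narrower objections are fair:

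- Section 2.4 never says its alpha is two-sided. That is inferred from the calculation.
- A familywise rate above 99% needs about 14 tests and a correlation no higher than about 0.7. If the time-by-group analysis is read as one test per measure, the rate is about 0.80 to 0.99 over the correlations shown. The point does not depend on this figure.
- The registry record and the analysis code were not available, so nothing can be said about what they contain.

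None of these removes the contradiction or changes which value the article supports.

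**Conclusion.** The concern holds, and the threshold must be corrected. The analysis rule and the sample-size alpha differ tenfold. As printed, the rule carries a 50% type I error per test in place of 5%, and with 27 per arm it would accept an observed difference of 0.18 SD in place of 0.55 SD. The 50% figure follows from the definition of a p-value and needs no assumption. The SD figures assume a two-sample t-test with 27 per arm. The COPM-point figures also assume the implied SD of 2. The conclusion that two-sided 0.05 was intended rests on its reproducing the stated 27 per arm, which neither 0.5 nor one-sided 0.05 does.

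**What to change.** In section 5.3, replace the printed threshold with two-sided p < 0.05. In section 2.4, add that the 5% alpha is two-sided, so that the two sections agree explicitly. Then check that the full protocol, the analysis plan, the analysis code and the registry record carry the same value. This is a consistency check only, since none of them was seen.

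The cost is one inserted digit and one added word, issued as a correction to the published article. Sample size, design and conduct do not change.
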